#### Staff training

Prior to recruitment commencement, a meeting will be scheduled in each center to introduce the study to unit staff. This session will include:

Brief presentation on study aims and eligibility criteria.Introduction to oral and written informed consent process.Presentation of data collection platform and its requirements.NEC diagnosis guidelines for Radiologists and Ultrasonographers (if requested).

A subsequent meeting will take place two weeks after initiating the study. Staff will be asked about any problems they might be experiencing with implementing the study, such as patient recruitment, data collection and NEC diagnosis.

Multi-center research meetings will be held two times a year for the first 2 years to improve adherence to study protocol, improve recruitment rates and resolve on-going issues.

All data will be collected on a secure electronic database and will be available on request.

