### Blinding (masking)

Assessments regarding the clinical course will be conducted by an assessor blind to treatment allocation. Due to the nature of the intervention staff cannot be blinded to allocation but are strongly inculcated not to disclose the allocation status of the participant at the follow up assessments. A member of the research team blinded to treatment allocation will feed data into REDCap.

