#### Primary outcome

Patients will be evaluated for NEC based on the presence of at least three of the following clinical symptoms (37–40).

Abdominal distention.Visible bowels loops.Feeding intolerance (defined as emesis ≥2 consecutive feeds, or gastric residuals of >50% per feed in ≥2 consecutive feeds, bilious residuals, bilious emesis).Temperature instability (defined as ≥2 consecutive measurements).Frank bloody stools.Cardiovascular instability (hypotension; defined as MAP <30 mmHg, tachycardia >160/' or bradycardia <80/').Recurrent apnoea.Increase of abdominal girth > 2 cm (allowing inter-observer variability of 1 cm) within 12 hAbdominal wall erythema.

And/or at least 2 of the below laboratory findings based on Walsh and Bell criteria (modified by Kliegman) (25, 37).

Thrombocytopenia < 50 kLeukopenia <6 kCRP > 10 mg/dlPCT > 1 IU/lCoagulopathy.

NEC will be diagnosed using the abdominal ultrasonography (AUS) or plain abdominal radiography (AR).

Gray- scale AUS will be used to assess bowel wall echogenicity, measure bowel wall thickness, peristalsis, pneumatosis intestinalis (PI), portal vein gas (PVG), free abdominal air and fluid. The following finding on AUS will be equivalent do NEC (41):

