1. A bowel wall thickness of >2, 7 mm accompanied by an increase in echogenicity will be considered as suspicious. Color Doppler (CD) ultrasound will be required to evaluate blood flow in the superior mesenteric artery (SMA), and bowel wall perfusion (BWP). Evaluation of BWP; three categories of flow in the bowel wall will be recognized in color Doppler: *normal* (1–9 CD signal dots per cm^2^), *increased* (“zebra” pattern, “Y” pattern or “ring” pattern), and *absent* (when no color Doppler signals will be present) which will be reported as transmural necrosis.2. Bowel wall thickness below 1.0 mm will be considered as abnormal thinning because of ischaemia or necrosis. Measurements will be recorded in relaxed bowel segments.3. PI will be defined as small intramural hyperechoic focuses in the bowel wall, which will not change position despite peristalsis, respiratory movement, or abdominal compression with the transducer.4. Abnormal peristaltic contractions of the small bowel will be defined as <10 movements/min.5. For evaluation of PVG, the portal vein will be adjusted in a transverse or longitudinal section of the liver. PVG will be defined as highly echogenic round particles with a diameter of approximately 1 mm registered within portal circulation.6. Using a transverse section of the right upper abdomen showing the liver just below the diaphragm, free abdominal gas will be detected as a bright echogenicity between the abdominal wall and the anterior surface of the liver.7. Free abdominal fluid will be evaluated as an hypoechogenic material between the bowel loops.

To assess the SMA flow the transducer will be held in the longitudinal section just below the xiphoid. Elevated systolic velocities (up to100–120 cm/s), and high diastolic velocity will be suspicious for NEC.

Ultrasonographer experience will vary between centers (5 to 20 years of experience). All examinations will be performed at the bedside and saved on a secure web-based platform. No specific pre-test requirements will be required.

Plain AR using a vertical and horizontal beam will be repeated every 12–24 h as the disease tends to progress rapidly (42). The following plain abdominal radiography findings will be considered typical for NEC:

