PI is most commonly present in the distal small bowel and large bowel, hence it is usually seen in the right lower quadrant, although it may be present in any part of the gastrointestinal tract (43, 44).PVG as an extension of intramural gas present in bowel wall veins, passing into the portal vein system (28, 29).*Free intraperitoneal gas* as a result of bowel perforation, which usually is in the distal ileum and proximal colon. It is the only universally accepted radiologic indication for surgical intervention (12).

We will define *AUS as positive for NEC* when three of the following findings are appreciated on examination (41):

1. Abnormal bowel wall thickness (<1.0 mm or >2,7 mm)2. PI3. Free abdominal fluid as a focal fluid collection4. Abnormal SMA blood flow, or bowel wall perfusion.

And one of the listed findings:

1. Free abdominal air2. Delayed peristalsis3. PVG.

AR will be classified *as positive for NEC*, if one of the following findings will be present (23):

Intramural gas (pneumatosis intestinalis)Portal venous gasFree intraperitoneal gas

*And*

Bowel dilatation.

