#### Interim analyses

Our study is a multicentre study, located in 4 different unit. Three interim analyses (IA) will be performed on the primary end point every 100 recruited patients. IA will be conducted by an independent statistician, blinded for the treatment allocation. This will allow us to track trial data collected on case report forms and generate performance metrics. Additionally, it will make data and study information available in a timely manner and re-estimate the sample size if needed. Results of interim analyses will be reported to the DMC, which will decide whether the trial should be continued or stopped for futility based on the pre-specified criteria. The Peto approach will be used: the trial will be ended using symmetric stopping boundaries at *P* < 0.001 (56).

Additionally, sensitivity analysis for the primary outcomes will be carried out with an intention-to-treat (ITT) approach. Protocol deviations will be reviewed by a blinded adjudication DMC who will decide by consensus whether a patient should be included in the ITT or per protocol population. We do not plan any subgroup analyses. In case of missing data, standard data imputation algorithms will be used (e.g., multiple imputation) (55).

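### Instruction in the NEC imaging criteria is optional for the readers whose images decide the primary endpoint, and no stated central reading or event adjudication backs it up

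*Protocol article*

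**What the plan says.** All references are to the Protocol article.

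- **Staff training.** A meeting in each centre before recruitment covers aims and eligibility, the consent process, the data platform, and "NEC diagnosis guidelines for Radiologists and Ultrasonographers (if requested"). Only the last item is conditional. A second meeting follows two weeks after the start: "Staff will be asked about any problems they might be experiencing with implementing the study, such as patient recruitment, data collection and NEC diagnosis". Multi-centre meetings take place twice a year for the first two years.
- **Primary outcome (Data collection and management).** Imaging decides the diagnosis: "NEC will be diagnosed using the abdominal ultrasonography (AUS) or plain abdominal radiography (AR"). Ultrasound is positive "when three of the following findings are appreciated on examination", from a list of four, together with one of three further findings. The component findings use cut-offs for wall thickness, peristalsis and colour Doppler signals. A radiograph is positive with intramural, portal venous or free gas, together with bowel dilatation.
- **Same section, on images.** Ultrasound scans are kept: "All examinations will be performed at the bedside and saved on a secure web-based platform".
- **Same section, on operators.** Their background is not uniform: "Ultrasonographer experience will vary between centers (5 to 20 years of experience").
- **Blinding (masking).** "Assessments regarding the clinical course will be conducted by an assessor blind to treatment allocation".
- **Interim analyses.** The only adjudication described concerns deviations and analysis populations: "Protocol deviations will be reviewed by a blinded adjudication DMC who will decide by consensus".

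**The concern.** The optional item is the one that teaches readers how to call the primary endpoint. Years of general experience do not replace instruction in a specific multi-item rule, and a reader who misapplies the rule without knowing it has no reason to request the session.

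If centres call NEC differently, the primary endpoint gains misclassification. When that error is the same in both arms, the observed difference shrinks towards zero. This costs power for the superiority comparison. It could also help to hide a true increase in NEC, which matters because the Objectives include showing that the feeding protocol does not raise NEC risk.

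The optional wording is a choice stated in the article, not a detail left to a fuller document.

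**Working it through.** **1. Is the written rule enough without instruction?** Reading the sections side by side shows where two competent readers could part.

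- Outcomes defines Stage II and III by a distended abdomen with intramural and/or portal gas. Under the ultrasound rule, abnormal wall thickness, focal free fluid and abnormal mesenteric flow, plus delayed peristalsis, make a positive examination with no gas at all.
- The ultrasound findings are introduced as equivalent to NEC. The first of them is then called only suspicious, and the final rule needs three findings plus one.
- The mesenteric systolic velocity is given as a range with an upper limit, which is not a clear cut-off.

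**2. Do the other safeguards cover the gap?**

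- Blinded assessment protects against differences between arms, not between centres. It names the clinical course and does not mention imaging readers.
- Stored examinations would make central reading possible, but none is stated.
- Adjudication covers deviations and population membership, not NEC events.
- The later meetings depend on staff raising a problem, after recruitment has begun.

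**3. Reproducing the plan's sample size.** Inputs from Sample size: 18% v 7.6%, power 80%, significance level 5%, 20% loss, 192 per arm. The two-sided test is from Statistical methods (two-sided 95% confidence interval).

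n = [1.96·√(2·p̄(1−p̄)) + 0.8416·√(p1(1−p1) + p2(1−p2))]² / (p1−p2)², with p̄ = (0.18 + 0.076)/2 = 0.128. This gives 160.8, so 161 per arm; the unpooled version gives 159. Multiplying by 1.2 gives 194 or 191, which brackets 192. Because 192/1.2 = 160, I take 160 as the evaluable number per arm and 192 as the number with no loss. (Taking 20% off 192 leaves 154, with power 78%.)

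**4. Power with perfect reading.** Power = Φ[(|p1−p2| − 1.96·SE0)/SE1], where SE0 = √(2p̄(1−p̄)/n) and SE1 = √((p1(1−p1) + p2(1−p2))/n).

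- n = 160: (0.104 − 1.96 × 0.03735)/0.03690 = 0.83, power 79.8%.
- n = 192: power 86.5%.

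**5. Power with assumed reading error, equal in both arms.** Sensitivity (Se), specificity (Sp) and the fraction f of infants without NEC who are imaged are all assumptions.

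Observed rate = p·Se + (1−p)·(1−Sp)·f

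For Se 0.95, Sp 0.98, f = 1:
- control: 0.18 × 0.95 + 0.82 × 0.02 = 0.1874
- study: 0.076 × 0.95 + 0.924 × 0.02 = 0.0907
- difference: 9.7 points instead of 10.4
- n = 160: (0.0967 − 1.96 × 0.03868)/0.03830 = 0.55, power 70.7%

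| Se / Sp | f | Observed rates | Power, 160 per arm | Power, 192 per arm |
|---|---|---|---|---|
| 1 / 1 | – | 18.0% v 7.6% | 80% | 86.5% |
| 0.95 / 0.98 | 1 | 18.7% v 9.1% | 71% | 78% |
| 0.95 / 0.98 | 0.3 | 17.6% v 7.8% | 75% | 83% |
| 0.95 / 0.98 | 0.1 | 17.3% v 7.4% | 77% | 84% |
| 0.90 / 0.95 | 1 | 20.3% v 11.5% | 58% | 66% |
| 0.90 / 0.95 | 0.3 | 17.4% v 8.2% | 69% | 77% |

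False positives drive much of the loss because most infants do not have NEC. The result therefore depends strongly on how many of them are imaged.

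**The case against.** The strongest reply is that the talk is optional but the rule is not. The same written criteria, with numerical cut-offs, bind all four centres. Diagnosis may also rest on a radiograph, whose rule is short, and surgically verified cases need no radiology. The two-week meeting asks about NEC diagnosis specifically, further meetings follow, examinations are stored, and clinical assessment is blinded. All of this stands and lowers the risk. It does not remove it, for the reasons in steps 1 and 2 of the working.

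The reply is also right about the power figures:

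- They rest on assumed accuracy.
- They compare with perfect reading, which training would not achieve.
- With f = 1 they apply false positives to every infant, although evaluation for NEC starts from clinical symptoms and/or laboratory findings.
- The 18% and 7.6% come from reported incidence, which may already contain reading error.

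A reader might infer more than the documents support:

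- *That NEC will be read to different standards.* No section says so; it is a risk.
- *That radiologists' experience also varies.* The statement concerns ultrasonographers only, and its lower end is five years.
- *That the comparison will be biased.* Error equal in both arms dilutes the difference. Centre is not a listed stratum and imaging readers are not named as blinded, so balance is not guaranteed, but nothing points to a systematic difference between arms.

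Reader manuals and scoring forms do commonly sit outside an article, so their absence is not part of this point.

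**Conclusion.** The point holds as a modest weakness that is cheap to correct. The plan makes instruction in the primary-endpoint imaging criteria optional, while ultrasonographer experience varies between centres and no central reading or NEC adjudication is stated. That leaves avoidable room for inconsistent calls between centres.

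The illustrated cost, at 95% sensitivity and 98% specificity, is 3 to 9 percentage points of power at 160 per arm (80% to between 77% and 71%) and about 3 to 8 at 192 (86.5% to between 84% and 78%). These figures assume error equal in both arms and true rates of 18% and 7.6%. They show what reading error of that size would cost. They do not estimate the harm done by optional training or the gain from making it compulsory; the share that training would recover is unknown.

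**What to change.** In Staff training, delete the words that make the NEC-criteria session available only on request. Require every radiologist and ultrasonographer who will read trial images to complete it before the site opens, and any new reader before the first trial read.

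A short scoring form listing the ultrasound and radiograph items, stored with the images, would be a useful but optional addition.

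The cost is one wording change and some reader time at four sites. The centre meeting is already scheduled, and no procedure, extra reader or burden on the infants is added.

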#### Plans to promote participant retention and complete follow-up

All randomized infants who are prematurely discontinued from study drug will be considered *off study intervention/on study*. They will follow the same participant timetable as those infants who continue study intervention. All these infants will be followed through 12 months as scheduled.

Once an infant is enrolled or randomized, the study site will make every reasonable effort to follow the infant for the entire study period. It is projected that the rate of loss-to-follow-up on an annual basis will be at most 20%. Each study site staff will develop and implement local standard operating procedures to achieve this level of follow-up.

#### Data management

Study data will be collected and managed using REDCap (45, 46), an electronic data capture tools hosted at [Princess Anna Mazowiecka's Hospital MUW]. REDCap is a secure, web-based software platform designed to support data capture for research studies, providing (1) an intuitive interface for validated data capture; (2) audit trails for tracking data manipulation and export procedures; (3) automated export procedures for seamless data downloads to common statistical packages; and (4) procedures for data integration and interoperability with external sources (41, 42).

Data integrity will be enforced through a variety of mechanisms. Referential data rules, valid values, range checks, and consistency checks against data already stored in the database (i.e., longitudinal checks) will be supported. Modifications to data written into the database will be documented through either the data change system or an inquiry system. Data entered in the database will be retrievable for viewing through the data entry applications. The type of activity that an individual user may undertake will be regulated by privileges associated with his/her user identification code and password. A complete back up of the database will be performed twice a month.

#### Confidentiality

Complete patient and study information will be stored on REDCap. Only researchers involved in the study will be provided with a personalized login and password to access the study information. The statistical team will not have access to sensitive data such as date of birth, address, contact details. All records containing the above patient details and relevant medical history will be stored separately in a locked file cabinet.

#### Plans for collection, laboratory evaluation and storage of biological specimens for genetic or molecular analysis in this trial/future use

Not applicable.

### Statistical methods

#### Statistical methods for primary and secondary outcomes

As the trial is designed as a superiority study, both primary and secondary outcomes will be analyzed based on the per-protocol (PP) approach.

For primary outcomes and dichotomous secondary outcomes, between-group differences, and the two-sided 95% confidence interval (CI) for the estimated difference approach will be used (47–49).

For continuous outcomes, means/medians and 95% CIs will be calculated. Differences in changes from baseline between treatment groups will be compared using a two-sample t test or Mann-Whitney *U*-test (50).

Additionally, a predictive model to clarify the risk of NEC complications in both study groups will be implemented. Statistical and machine learning techniques such as decision trees, random forests, and support vector machine (SVM) will be used (51–55).

All statistical calculation will be carried out using R package (The R Foundation Vienna, Austria) and Statsoft (Hamburg, Germany).

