**Data collection**								
Baseline demographics	x							
VIS	x	x	x	x				
Protein and caloric intake	x	x	x	x				
days on mechanical ventilation	x	x	x	x				
CLABSI		x	x	x				

CLABSI, central line associated blood stream infection; VIS, vasoactive inotropic support score.

This study is designed as a randomized, parallel-group, superiority multi-center trial, with an 1:1 allocation and stratification by type of lesion.

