### Criteria for modifying or discontinuing allocated interventions

In infants who present with *one or two* of the following symptoms such abdominal distention, visible bowels loops or feeding intolerance (defined as emesis ≥2 consecutive feeds, or gastric residuals of >50% per feed in ≥2 consecutive feeds, bilious residuals, bilious emesis) the intervention will be **modified** by decreasing enteral nutrition by 50% and substituting the remaining fluid requirements with adequate parenteral nutrition for a **maximum** of 48 h. If symptoms persist above 48 h, the trial will be discontinued.

The trial will be **discontinued** if the following occur:

The patient presents with at least three of the following symptoms.

Abdominal distention.Visible bowels loops.Feeding intolerance (defined as emesis ≥2 consecutive feeds, or gastric residuals of >50% per feed in ≥2 consecutive feeds, bilious residuals, bilious emesis)..Temperature instability (defined as ≥2 consecutive measurements).Presence of bowel perforation of NEC confirmed on abdominal x-ray or ultrasound.

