### Outcomes

#### Primary outcomes

##### Necrotizing enterocolitis and death related to NEC

The primary outcomes will include Stage II or III of NEC as defined by Kliegman and Walsh (25) and death related to NEC.

Stage II NEC will be defined as distended abdomen and radiological symptoms (intramural and/or portal gas). Stage III NEC will be defined as distended abdomen, radiological symptoms (intramural and/or portal gas) and respiratory and cardiovascular failure requiring mechanical ventilation and inotropic support (25). In surgery verified cases no radiological verification will be required.

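### Superiority is given as the reason for a per-protocol primary analysis, ITT is reduced to a sensitivity analysis with adjudicated membership, and nothing stops the per-protocol set from dropping NEC events

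*Protocol article*

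**What the plan says.** All places are in the protocol article.

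- **Design** (Trial design, below Table 1): "This study is designed as a randomized, parallel-group, superiority multi-center trial".
- **Primary analysis set** (opening sentence of the Statistical methods section): "As the trial is designed as a superiority study, both primary and secondary outcomes will be analyzed based on the per-protocol (PP) approach".
- **Role of ITT** (Interim analyses): "sensitivity analysis for the primary outcomes will be carried out with an intention-to-treat (ITT) approach". Secondary outcomes are not mentioned there.
- **Who decides membership** (Interim analyses): protocol deviations go to a blinded adjudication DMC, "who will decide by consensus whether a patient should be included in the ITT or per protocol population". Interim results are also reported to the DMC (Interim analyses; section on the DMC and TSC).
- **Endpoint** (Primary outcomes): "The primary outcomes will include Stage II or III of NEC as defined by Kliegman and Walsh (25) and death related to NEC".
- **Discontinuation** (Criteria for modifying or discontinuing allocated interventions): one or two signs lead first to modification, and to discontinuation if they last beyond 48 h. Otherwise the rule is "The patient presents with at least three of the following symptoms". The list that follows is distention, visible loops, feeding intolerance, temperature instability and "Presence of bowel perforation of NEC confirmed on abdominal x-ray or ultrasound".
- **After discontinuation** (Plans to promote participant retention and complete follow-up): the infant stays on study. "All these infants will be followed through 12 months as scheduled".

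**The concern.** In a superiority trial, the comparison of all randomised infants as allocated is the one that randomisation protects. A per-protocol set is selected after randomisation, so its two arms need no longer be comparable. The plan uses the superiority design to justify the weaker set.

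Two features make this more serious than a slip of wording. First, the infants most likely to come off the allocated feeding are those with NEC or signs that raise suspicion of it. If they leave the per-protocol set, the primary analysis loses events it is meant to count. Second, the ITT analysis is not a clean safeguard, because its membership is itself decided infant by infant. ITT membership follows from randomisation and leaves nothing to adjudicate.

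At stake is the main conclusion. The trial also aims to show that faster, protocol-based feeding does not raise NEC risk. Losing study-arm cases could produce an apparent benefit or hide harm.

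**Working it through.** **1. Overlap between stopping rules and endpoint.**

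| Discontinuation item | Endpoint definition (stage II/III) | Triggers NEC work-up |
|---|---|---|
| Abdominal distention | yes, together with radiological signs | yes |
| Visible loops | no | yes |
| Feeding intolerance | no | yes |
| Temperature instability | no | yes |
| NEC or perforation confirmed on imaging | in substance, yes | not applicable |

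The work-up (Data collection and management, Primary outcome) uses the same threshold of at least three signs, from a longer list. The discontinuation section does not make clear whether confirmed NEC or perforation suffices alone or counts as one of the three items.

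**2. Scope for unequal exclusion.** Control feeding is at the physician's discretion, including slowing or withholding (Control group). Study feeding has set start, advancement and goal rules (Study group). Feeding deviations are thus easier to define in the study arm.

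**3. The plan's own figure.** Inputs (Sample size): 18% v 7.6%, 80% power, 5% level, 20% loss, 192 per group. The two-sided unpooled formula is

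n = (1.96 + 0.84)² × [0.18×0.82 + 0.076×0.924] / 0.104², which gives 159 per arm.

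159 × 1.2 = 191, against the stated 192. The figure reproduces. With 192 analysed per arm, power is 86.5%.

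**4. Effect of losing NEC cases.** Let f be the share of an arm's NEC cases left out of the per-protocol set. The documents give no value; 25% and 50% are assumed. The apparent rate is

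p_PP = p(1 − f) / (1 − pf), on 192(1 − pf) infants.

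*(a) Study arm only, true rate equal in both arms (no effect), two-sided 5% test:*

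| True rate | f | Study arm appears as | Control | False significance |
|---|---|---|---|---|
| 18% | 25% | 0.135/0.955 = 14.1% | 18% | about 17% |
| 18% | 50% | 0.09/0.91 = 9.9% | 18% | 61% to 62% |
| 7.6% | 25% | 0.057/0.981 = 5.8% | 7.6% | about 11% |
| 7.6% | 50% | 0.038/0.962 = 4.0% | 7.6% | about 33% |

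For 18% and f = 50%, the pooled standard error gives 61% and the unpooled one, which corresponds to the planned confidence interval, gives 62%. A harmful study-arm rate of 25% (assumed) with f = 50% would appear as 0.125/0.875 = 14.3%.

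*(b) Equal share in both arms.* If the true rates are equal, the per-protocol rates are equal too and the false-positive rate stays near 5%. The cost is power at the planning rates:

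| f | Apparent rates | Power |
|---|---|---|
| 0 | 18% v 7.6% | 86.5% |
| 25% | 14.1% v 5.8% | 77% |
| 50% | 9.9% v 4.0% | 61% |

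**The case against.** The strongest reply is that event removal is nowhere stated. Set membership is tied to review of protocol deviations, and stopping because the protocol requires it can be read as adherence. An infant stopped for confirmed NEC has already had the event on allocated feeding, so many per-protocol definitions would count it. The detailed definition may also stand in an analysis plan that is not shown. This stands: removal is a risk left open, not a rule.

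Four stronger readings are therefore not supported.

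- **That exclusions will fall mainly on the study arm.** The discontinuation section covers the allocated interventions without limiting itself to one arm. Imbalance is plausible, not established.
- **That every stopping sign is part of the endpoint, or that any one sign ends the intervention.** Visible loops, intolerance and temperature instability only prompt evaluation, and one or two signs lead first to modification.
- **That the 17% and 62% figures are the error to expect.** They describe one-arm exclusion with assumed shares; equal exclusion leaves the error rate near 5%.
- **That the DMC must be unblinded.** The interim statistician is blinded to allocation, so results could be presented by coded arm. A tension remains, because the DMC is also expected to judge whether the active intervention differs from control. Even full blinding to arm would not prevent exclusion that depends on the outcome.

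None of this answers the stated rationale for per-protocol, the reduced role of ITT, or the adjudicated ITT membership. These are explicit text, and no other section corrects them. An ITT sensitivity analysis could reveal a discrepancy, but it would not make the primary result valid.

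**Conclusion.** The choice of primary analysis set is wrong as written and must be changed. That conclusion needs no assumption about who is excluded.

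The possible loss of NEC events is a further risk, which the text permits but does not prescribe. Its size depends on the share of cases dropped and on whether the arms are affected alike. For assumed shares of 25% and 50%, it runs from lost power (86.5% to about 77% and 61%) under equal exclusion to false significance of about 17% and 62% under study-arm-only exclusion at a true 18%. All these figures take 192 infants per arm before exclusion.

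**What to change.** - **Statistical methods for primary and secondary outcomes:** make ITT the primary analysis of primary and secondary outcomes. It includes every randomised infant in the allocated arm, with NEC counted regardless of modification or discontinuation. Per-protocol becomes supportive. Remove superiority as the reason for per-protocol.
- **Interim analyses:** delete adjudication of ITT membership. Have per-protocol exclusions decided before unblinding by people who have not seen interim results. State that NEC, its signs and discontinuation under the protocol's criteria are never reasons for exclusion.
- **Recruitment:** state that the target of 192 valid observations per arm does not mean per-protocol-evaluable infants, so that excluded infants are not replaced.
- **Discontinuation criteria:** reconcile the text on whether confirmed NEC or perforation stands alone or is one of the three items. Which reading is right is for the investigators.

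The cost is wording in the protocol and analysis plan, through the amendment route the protocol describes. Discontinued infants are already followed to 12 months, so the planned follow-up provides the data for an ITT analysis. The sample size need not change.
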